### Randomization

2.7

Based on a computer-generated randomization list (nQuery Advisor 6.01, Janet D. Elashoff), opaque, numbered envelops are produced at the Coordinating Centre for Clinical Trials. These envelopes contain the randomization result with the assignment to treatment group A or B (see Fig. 1). They are opened in ascending order after the consent of the patient/guardian has been obtained. The study doctor must note the patient identification number and the date and time of the randomization and confirm by his signature.

### Statistical analysis

2.8

A list of imaginable complications and risks with possible management plans is part of the study protocol. In case of changes in the treatment due to complications or patient requests, patients can be treated accordingly in our clinic. All randomized patients who will be treated with the silicone finger cap or the film dressing will be included in the intent-to-treat-analyses.

The primary objective of the study is to verify the hypothesis that the silicone finger cap is superior to the conventional film dressing in regards to its acceptance by the patients/guardians. The primary endpoint is the rate of patients who decide up to day 28 to continue their treatment with the silicone finger cap. If this rate is at least 80% and the lower limit of the confidence interval is not less than 65%, the silicone finger cap is considered to be much better accepted than the conventional method.

The secondary target parameters are exploratively evaluated. Secondary endpoints are analyzed according to their scale level: for steady endpoints, mean and standard deviation, or medians and quartiles (graphically corresponding to confidence intervals or boxplots), for the categorical endpoints absolute and appropriate relative frequencies are used. Depending on the distribution of the variables to be analyzed the *t* test, the *U* test and the Chi test^[2]^ are used. For paired comparisons, the paired *t* test is used in the case of normally and the Wilcoxon test in the case of nonnormally distributed variables. Sub-group analyses according to patient age, injury severity, and mechanism of injury will be performed if possible. The statistical analysis is carried out using the SPSS program system (International Business Machines Corp. [name]) and the SAS System (SAS Institute Inc., [name]) for Windows program in the currently available versions.

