### Study design

2.1

This pilot study is a monocentric, prospective, randomized, controlled clinical trial. Primarily, it will investigate the acceptance of the silicone finger cap in comparison to conventional film dressings. Using sealed neutral envelopes prepared by external staff from the Coordinating Centre for Clinical Trials, our patients will be randomly assigned by the study doctors to begin their treatment either with the finger cap or the film dressing. After 2 weeks they will be changed to the other treatment modality. After another 2 weeks have passed, patients/guardians will have to decide prior to the dressing change which treatment they would like to receive thereafter if further occlusion is needed. The primary clinical endpoint of this pseudo-cross-over study (Fig. 1) is the rate of patients/guardians who decide to continue their treatment with the silicone finger cap. Further secondary endpoints include the determination of the safety of the finger cap in comparison to the film dressing and the determination of disease-specific quality of life during the treatment with the silicone finger cap in comparison to the film dressing using a modified quality of life Wuerzburg Wound Score regarding pain during application and treatment with the finger cap, restrictions in daily activities and quality of life.^[14]^ Also the necessity of unplanned dressing changes in comparison to the film dressing and changes in microbiological colonization in the wound during the treatment will be registered. Additionally, we will measure the reepithelialization rate and determine the tissue growth at 28 days and at 4 months after the injury. We will also test the function of the regenerated perspiratory glands and the clinical outcome in terms of sensitivity and motility of the injured fingertip as well as cosmetic aspects.

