### Inclusion and exclusion criteria

2.4

The participants are recruited by trained surgeons in the Emergency Department of the University Hospital Carl Gustav Carus at the Technische Universität Dresden, Germany. We include male and female patients older than 2 years with full skin substance defects distal to the distal interphalangeal joint unsuitable for primary surgical closure without further substance loss. No more than 5 fingers per patient may be injured. Patients must have a circumference of the proximal phalanx in between 3.0 and 9.0 cm. In addition, a signed written informed consent must exist.

We exclude the participation of any patient with known hypersensitivity against medical silicone or self-adhesive films. Further exclusion criteria are bony injuries requiring a surgical intervention, bite injuries, or chronic dermatological disorders of the hand. Furthermore, intake of medications affecting wound healing, such as systemic (noninhalative) glucocorticoids, immunosuppressive, or blood-thinning medications are exclusion criteria. Patients with a known wound healing disorder are also excluded from this clinical trial. In addition, ongoing or recently finished chemotherapy, immunodeficiencies or diabetes mellitus, are exclusion criteria. In accordance to §20 of the German Medical Device Act, pregnant or breastfeeding women, as well as any women, when a pregnancy at the beginning or during the course of the study cannot be ruled out (ie, not postmenopausal, no bi-lateral oophorectomy or hysterectomy, no contraceptive method with pearl index less than 1%, no sexual abstinence, or partner with vasectomy) will have to be excluded. Beyond that, patients who are suffering from an addiction or other diseases, which do not allow them to assess the entity, scope, and possible consequences of this clinical trial are also excluded. The same applies for patients who are not cooperative or who already participated in other clinical trials within the last 4 weeks.

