#### Proposed sample size

2.6.1

There is no certified medical device available for the conservative management of fingertip amputation injuries. Opsite Flexigrid (Smith & Nephew Medical Limited, Hull, England) has not been certified for full thickness amputations injuries as described, and our novel finger cap has never been used before in a controlled trial. Therefore, this study is per definition a pilot study that has to be limited to a small sample size in order to comply to German and European legislation as well as to guidelines of good clinical practice.

The primary objective is the rate of patients who decide for the silicone finger cap at day 28. At this point they have experienced both methods (conventional film dressings and silicone finger cap) for 2 weeks each. This rate can be regarded as a measure of the acceptance of the silicone finger cap. If 80% of the patients in this study decide for the silicone finger cap we consider the hypothesized superiority of the finger cap as verified. Assuming that approximately 80% of the patients decide for the silicone finger cap, 20 patients (95% confidence interval, one-sided, 65% lower limit, the distance from the rate to the lower limit of the confidence interval is at most 15%) are needed (Program nQuery-Advisor 6.01, Copyright^©^ 1995–2005, Janet D Elashoff). When considering 2 possible drop-outs, 22 patients must be included.

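### Unpaired comparisons of exploratory continuous outcomes use only unadjusted t or U tests; one pre-specified baseline size covariate for tissue growth would probably add precision at about 11 per group (minor)

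*Protocol article*

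**What the plan says.** Section 2.8 (Statistical analysis) sets the status of these endpoints: "The secondary target parameters are exploratively evaluated". It then lists tests by scale and distribution: "Depending on the distribution of the variables to be analyzed the *t* test, the *U* test and the Chi test". A separate sentence covers the other case: "For paired comparisons, the paired *t* test is used in the case of normally and the Wilcoxon test in the case of nonnormally distributed variables". The first list is therefore the one for unpaired comparisons, and none of its tests uses a starting value. Baseline factors come in at one place only: "Sub-group analyses according to patient age, injury severity, and mechanism of injury will be performed if possible".

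Section 2.1 (Study design) names the healing outcomes: "we will measure the reepithelialization rate and determine the tissue growth at 28 days and at 4 months after the injury". Section 2.4 sets the size limits for entry: "Patients must have a circumference of the proximal phalanx in between 3.0 and 9.0 cm". It admits patients older than 2 years and states no upper age limit. Section 2.5 (Procedure) has photographs taken at each visit, to be turned into 3-D models from which the progress of finger volume is measured. It also has every patient change dressing on day 14.

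**The concern.** The eligibility limits allow a three-fold range in finger circumference. For fingers of similar shape that is up to 9-fold in area and 27-fold in volume. If finger size or the amount of tissue lost helps determine how much tissue regrows, an unadjusted comparison leaves that variation in the error term. It also lets a chance difference in starting size pass into the estimate. At about 11 patients per group, chance differences are not small.

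The article says that the secondary data are to help plan definitive studies, so the precision of these estimates matters even though they are exploratory. Age and severity are used only to split about 22 patients into sub-groups, which is an inefficient use of baseline information.

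**Working it through.** **The plan's own sample size.** Section 2.6.1 gives "20 patients (95% confidence interval, one-sided, 65% lower limit, the distance from the rate to the lower limit of the confidence interval is at most"; the margin is 15 percentage points and the expected rate 80%. A one-sided Wald interval gives n = 1.645² × 0.8 × 0.2 / 0.15² = 19.24, rounded up to 20. Then "When considering 2 possible drop-outs, 22 patients must be included": 20 + 2 = 22. The figure reproduces. It sizes a single proportion and does not depend on how healing is analysed.

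**Inputs.** 22 / 2 = 11 per group; the 1:1 ratio is an assumption, since the article does not state it. Also assumed are two-sided 5%, 80% power, and a correlation r between the baseline covariate and the outcome as analysed. The documents give no r, so a range is shown.

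**Unadjusted t test.** Noncentral t with 2n − 2 = 20 df and noncentrality d / √(2/11). Solving for 80% power gives d = 1.256 SD.

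**ANCOVA with one covariate.** The variance is multiplied by (1 − r²) × (1 + 1/(2n − 4)) = (1 − r²) × (1 + 1/18), with 19 df. The second factor is the average cost of chance imbalance in the covariate.

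| r | variance ratio | detectable difference | equivalent unadjusted N = 22 × (1.256/d)² |
|---|---|---|---|
| 0 | 1.06 | 1.294 SD | 20.7 |
| 0.3 | 0.96 | 1.234 SD | 22.8 |
| 0.5 | 0.79 | 1.121 SD | 27.6 |
| 0.7 | 0.54 | 0.924 SD | 40.6 |

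**Break-even.** The variance ratio equals 1 when r² = 1 − 18/19 = 0.0526, so r is about 0.23. Counting the lost degree of freedom as well, r² = 1 − (1.256/1.294)² = 0.058, so r is about 0.24. Below that, adjustment costs precision.

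**More covariates.** With k covariates the second factor becomes 1 + k/(2n − k − 3), with 20 − k df. At a joint R of 0.3 the detectable difference is 1.274 SD with two covariates and 1.318 SD with three. Both are worse than 1.256 SD with none.

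**Chance imbalance.** The SD of a standardised baseline difference is √(2/11) = 0.426. The chance that it exceeds 0.5 SD in either direction is 24%. In simulation the unadjusted t test kept about 5% type I error over all trials. Among the 24% with an imbalance above 0.5 SD, it was about 10% (r = 0.5) or 14% (r = 0.7).

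**The case against.** The strongest objection is that nothing here is wrong. A t or U test after randomisation is valid, the endpoints are exploratory, and section 2.8 is a condensed paragraph of default tests. An analysis plan that is not shown could add a model. This stands, and it limits the point to a suggested improvement on the stated method.

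Several stronger readings are tempting, and the documents do not support them:

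- **That healing is definitely tested between the randomised groups in this way.** Section 2.8 ties no test to any endpoint, and paired tests are also planned. After the switch each patient has used both dressings, so a test of tissue growth by randomised group would have to be unpaired. That is an inference from the design, not a statement in the article.
- **That the false-positive rate is 10% or 14%.** Those figures hold only within trials that happen to be imbalanced; the overall rate is about 5%.
- **That power is cut several-fold.** If the outcome is raw size proportional to finger cross-section (30% residual spread, true 40% effect, circumferences filling 3 to 9 cm), power is 20% unadjusted v 70% adjusted. But that model assumes the answer. Divide the same outcome by cross-section and an ordinary t test has 69% power v 68% for ANCOVA on the log scale. The article speaks of a rate, of growth and of volume progress, which may already be relative to the patient's own start. Also, 3.0 to 9.0 cm are eligibility limits, not an observed spread.
- **That day-0 defect size is on record.** Only age and circumference are firmly known at entry. A day-0 image is implied by photography at each visit, but no day-0 defect measurement is named. Circumference measures finger size, not tissue lost.
- **That adjustment would give a better device comparison at day 28 or 4 months.** By then the groups differ in the order of dressings, and adjustment does not change that.

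**Conclusion.** The point holds as a minor one. For unpaired comparisons of exploratory continuous outcomes the plan names only unadjusted tests, although a size measure is available at entry in a sample that may be very heterogeneous. The tests are valid on average. What is given up is precision, and only if baseline size correlates with the outcome above about r = 0.23: almost nothing at 0.3, a detectable difference of 1.12 instead of 1.26 SD at 0.5, and 0.92 SD at 0.7. This rests on 1:1 allocation, 11 evaluable patients per group, and an r that the documents do not give. If growth is analysed as change from the patient's own start, some of the size variation is already removed and the gain may be smaller.

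**What to change.** In section 2.8, add that where tissue growth (3-D volume) is compared between the randomised groups, the analysis is an ANCOVA with group and one pre-specified baseline size covariate. That covariate is the day-0 volume of the injured finger, or proximal-phalanx circumference if there is no usable day-0 image. Report the adjusted estimate with its 95% CI, and keep the t or U test as a sensitivity analysis.

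Three limits belong with it:

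- With 22 patients, do not add child/adult or severity terms.
- Do not apply a log-scale model to open wound area, which is zero once the wound has healed.
- State that after the day-14 switch the contrast is between treatment sequences, not devices.

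The cost is a few sentences of text and a few lines of code, with no new visits, patients or measurements beyond the volumes already planned. Statistically it costs one degree of freedom and a slight loss of precision if r is below about 0.23 (at worst 1.29 v 1.26 SD, at r = 0).

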### Procedure

2.5

Screening, recruitment, and treatment of our patients take place in our emergency department. Initially, the patient's medical history along with the accident history is obtained. All patients with fingertip amputations who present themselves to the emergency department are informed about this clinical trial. The injury is examined and the inclusion respectively exclusion criteria are checked. We routinely perform an X-ray examination to exclude bony injuries. Additionally women of childbearing age have to provide a pregnancy test prior to that. In case all inclusion and no exclusion criteria are fulfilled patients get comprehensively informed about the clinical trial and the informed consent is obtained by the trained surgeon. Randomization takes place through prepared nontransparent and consecutively numbered envelops and determines the initial treatment group (conventional film dressing or silicone finger cap). Afterwards, the respective occlusive dressing is applied according to the randomization result. We check the dressing 1 day after initial application for correct fitting. Afterwards we conduct clinical controls weekly to check for correct fitting of the occlusive dressing, to enquire possible adverse events and serious adverse events, and to take photos of the dressing and possibly of the wound. In case, the patient has got a silicone finger cap we aspirate wound fluid out of the reservoir to examine the microbiological colonization of the wound. If the patient has got an occlusive film dressing, no microbiological examination can be performed except for an initial smear and a 2nd smear when the film dressing is removed after 2 weeks. As a substudy of this clinical trial, excess wound fluid that is not used for microbiological analyses is preserved at −80 °C for future proteome analyses. Furthermore, patients are asked to complete a modified quality of life Wuerzburg Wound Score at each of their visits.

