On day 14 after the injury, the occlusive dressing method is changed. Patients treated with the conventional film dressing get a silicone finger cap and vice versa. Further 14 days later the patient decides which dressing she or he respectively the guardians would prefer for the remaining treatment if needed before the dressing is removed. The chosen treatment is then applied if further treatment is needed. At day 42 after the injury the treatment of the wound is orderly finished and the wound should be reepithelialized. The occlusive dressing is removed and photographs of the injury site are taken. If the wound is not fully epithelialized at this point, a conventional film dressing is used as long as further occlusion is needed. Final follow-up examination takes place 4 months after the injury. At the follow-up we test the function of the perspiratory glands and the regeneration of the fingerprint using Moberg Ninhydrin test.^[19]^ Also the range of motion in the distal interphalangeal, proximal interphalangeal and metacarpophalangeal joints, and the 2-point-discrimination threshold in the area of the injury is checked in comparison to the corresponding finger of the contralateral hand.^[20]^ Moreover, we also measure the soft tissue thickness above the bone in the region of the healed injury using medical ultrasound. Finally, patients have to complete a follow-up questionnaire. At each visit the dressing or, when applicable, the exposed finger is photographed from all perspectives. High definition photographs will be digitally analyzed and kept for documentation purposes. In this study, we will introduce a new volume-rendering method for monitoring finger growth 3-dimensionally. Photographs will be rendered in 3-dimensional models and advanced 3-dimensional segmentation, and filtering algorithms will be used to measure volume progress of the injured finger. This method will allow monitoring of tissue recovery in micrometers quality.

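### If the plain paired tests are meant for cap versus film, they ignore the healing between the two periods; a period-adjusted crossover test would use the same data better

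*Protocol article*

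**What the plan says.** Each patient uses both devices in randomised order. At day 14, "Patients treated with the conventional film dressing get a silicone finger cap and vice versa" (section 2.5, Procedure). On day 28, according to section 2.6.1, "At this point they have experienced both methods (conventional film dressings and silicone finger cap) for 2 weeks each".

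Several secondary endpoints in section 2.1 (Study design) are device contrasts. One is the "determination of disease-specific quality of life during the treatment with the silicone finger cap in comparison to the film dressing", which includes pain and limits on daily activity. Another reads "Also the necessity of unplanned dressing changes in comparison to the film dressing". The quality-of-life score is collected under both devices, since "patients are asked to complete a modified quality of life Wuerzburg Wound Score at each of their visits" (section 2.5).

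Section 2.8 (Statistical analysis) lists the t test, U test and chi-square test. For paired comparisons it adds that the paired t "test is used in the case of normally and the Wilcoxon test in the case of nonnormally distributed variables". It mentions neither period nor sequence and does not say which endpoints count as paired. It also says: "The secondary target parameters are exploratively evaluated".

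**The concern.** The injury is acute and the two periods are successive stages of its healing. The article itself expects this course: "At day 42 after the injury the treatment of the wound is orderly finished and the wound should be reepithelialized". Pain, daily restriction, quality of life and dressing problems may therefore differ between weeks 1-2 and weeks 3-4 whichever device is worn.

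Randomising the order does not take this out of a plain paired test. The cap-minus-film difference contains the period effect with a plus sign in one sequence and a minus sign in the other. With equal sequences the signs cancel in the mean but remain in the variance. With unequal sequences part of the period effect also stays in the mean.

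At stake are the secondary device comparisons and the standard deviations derived from them. The Introduction intends the secondary data to help plan later definitive studies, so an inflated SD or a shifted estimate would carry over into that planning.

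**Working it through.** **The plan's own figure.** The only sample size stated is for the primary endpoint: n = 1.645² × 0.8 × 0.2 / 0.15² = 19.24, rounded up to 20, plus 2 drop-outs = 22. This reproduces. No power or precision is stated for the paired secondary comparisons, so there is nothing further to reproduce.

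**Model.** For one patient, the cap-minus-film difference is d = τ + s·π + e. Here τ is the device effect, π the period effect, s = +1 or -1 by sequence, and e has SD 1. All effects are in units of that within-sequence SD. The documents give neither π nor τ. Assumed: π from 0 to 1.5 SD, τ = 0.65 SD, two-sided 5% level, additive effects.

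**Plain paired test**
- Bias of the mean: π × (n1 - n2)/N.
- Expected sample variance of d with equal sequences: 1 + π² × N/(N - 1). At N = 22 and π = 0.5 this is 1 + 0.25 × 22/21 = 1.262, an SD of 1.12. At π = 1 it is 1 + 22/21 = 2.048, an SD of 1.43. The true sampling error of the mean is still 1/√22 = 0.213, so the test uses a standard error that is about 12% or 43% too large.

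**Period-adjusted test**
- Estimate: the average of the two sequence means of d. π cancels whatever the split.
- Standard error: ½ × √[s²(1/n1 + 1/n2)], with pooled within-sequence variance s² and N - 2 degrees of freedom.

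**Power by simulation, 11:11, τ = 0.65**

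| Period effect | Paired t | Period-adjusted |
|---|---|---|
| 0 | 83% | 83% |
| 0.5 SD | 76% | 83% |
| 1 SD | 54% | 83% |
| 1.5 SD | 25% | 83% |

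The true size of the paired t test at 11:11 is 2.8% at π = 0.5 and 0.6% at π = 1. The adjusted test stays at 5%. The Wilcoxon test behaves like the paired t test.

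**Unequal sequences, N = 20, no device effect**

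| Split | Bias, π = 0.5 | Paired size, π = 0.5 | Bias, π = 1 | Paired size, π = 1 |
|---|---|---|---|---|
| 11:9 | 0.05 | 3.3% | 0.10 | 1.1% |
| 12:8 | 0.10 | 4.5% | 0.20 | 2.9% |
| 13:7 | 0.15 | 6.5% | 0.30 | 7.6% |
| 14:6 | 0.20 | 9.8% | 0.40 | 16.8% |

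For example, at 13:7 the bias is 1 × (13 - 7)/20 = 0.30 SD. The adjusted estimate is unbiased under this model, with size about 5% in every row.

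**How likely is imbalance?** The article gives neither allocation ratio nor blocking. If randomisation were simple (an assumption), 20 patients would split with a difference of at least 4 with probability 50%, and of at least 6 with probability 26%. Blocking would make this much rarer.

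**Price of adjusting when π = 0.** At 11:11 power is 82.6% paired against 82.4% adjusted. At 13:7 with τ = 0.66 it is 80% against 76%.

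**The case against.** Section 2.8 assigns no endpoint to any test. The range of motion and two-point discrimination in section 2.5 are compared with the contralateral finger, and there a paired test is right. The t and U tests that section 2.8 also lists are the very tests a period-adjusted analysis would use, if applied to period differences between sequences. The article does not say that they are used this way, but it does not rule it out. This stands, and it makes the point conditional. Cap versus film within patient is still the natural paired comparison in this design, and no other method is named for it.

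The article is condensed, and a full analysis plan may contain period and sequence terms. Their absence is therefore no finding. What can be challenged is the test that the article does name.

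A reader might infer that the trial is underpowered or that its device comparisons are biased. The documents do not support either reading. The affected endpoints are exploratory, with no level, power or decision rule attached, and the 0.65 SD device effect is this review's assumption. Bias arises only for an unequal split, and its sign depends on which sequence is larger. Up to 12:8 the size stays below 5% at both period effects tabulated. A period effect of a full SD is not documented either; at 0.5 SD and 11:11 the loss is 7 power points.

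Finally, the adjusted estimate is unbiased only without carry-over and without a device-by-period interaction. Devices are switched on day 14 of a healing wound and the article describes no washout, so this too is an assumption.

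**Conclusion.** The point holds conditionally and is a modest, inexpensive improvement. If the paired tests are meant for cap versus film, they are a poorer choice than a standard two-period analysis of the same data. With equal sequences the harm is lost power and a conservative test: small at a period effect of 0.5 SD and large at 1 SD. With unequal sequences the estimate also shifts, but a type I error above 5% needs marked imbalance, such as 13:7.

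That some period effect exists is inferred from the healing course in section 2.5. Its size, the device effect and the split are assumed. The primary endpoint is a single preference rate that uses none of these tests, so it and the sample size of 22 are untouched.

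**What to change.** State in section 2.8 or the analysis plan which comparisons are paired. For cap-versus-film contrasts, replace the plain paired tests with one of the following:
- a two-sample t test (Hills-Armitage) or U test comparing the period-1 minus period-2 differences between the two sequences; half the difference in sequence means estimates the device effect;
- a mixed model with device, period and sequence.

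State that either analysis assumes no carry-over and no device-by-period interaction. Keep the paired t and Wilcoxon tests for comparisons with the contralateral finger.

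The cost is a change of wording and one degree of freedom: under 1 power point at equal sequences and about 4 points at 13:7 if there is no period effect. No further data or patients are needed, and the SPSS and SAS systems already named suffice.
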